### Inclusion and exclusion criteria

Health plan members between 20 and 65 years of age with ICD-9 diagnoses indicative of non-specific low back pain will be eligible for the study if their pain has lasted at least three months, they rate their low back pain at least 3 on a 0 to 10 back pain bothersomeness scale, and give informed consent (Tables 1 and 2). Reasons for exclusion will be identified from two sources: 1) automated data on ICD-9 diagnoses recorded during all visits over the previous year made by health plan members identified with low back pain-compatible ICD-9 diagnoses, and 2) telephone eligibility interviews. Members found to have any of the following will be excluded: structural or neurologic causes or potential causes of low back pain (i.e., sciatica, underlying systemic or visceral disease, pregnancy, spondylolisthesis, spinal stenosis, cancer or unexplained weight loss, recent vertebral fracture); inappropriate candidate for massage (e.g., the chronic conditions identified in Tables 1 and 2); characteristics complicating the interpretation of findings (i.e., involved with litigation or compensation claim for back pain, evidence of severe or progressive neurologic deficits, back surgery within the prior three years, planning to seek other treatment for back pain); or characteristics related to ability to complete the study protocol (i.e., unable to speak or read English, plans to move out of town).

**Table 1 T1:** Inclusion Criteria

**Inclusion criteria**	**Rationale**	**Source***
Continuing member of Group Health	Defined population that is easy to identify, recruit and follow-up and who have been evaluated by a Group Health physician	A, TI

20 through 64 yrs of age	Chronic low back pain in children results from different causes than those we are studying; Older people have higher risk of undiagnosed serious conditions causing low back pain	A

At least one primary care visit for back pain within the past 3-12 months	Efficient method for identifying people who may have chronic low back pain	A

Non-specific, uncomplicated low back pain, i.e., these ICD-9 codes:	These codes are consistent with low back pain that is uncomplicated and mechanical in nature	A
		
724.2 Lumbago 724.5 Backache, unspecified 724.8 Other symptoms referable to back 846.0-9 Sprains and strains, sacroiliac 847.2 Sprains and strains, lumbar 847.3 Sprains and strains, sacral 847.9 Sprains and strains, unspecified site of the back		

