### Measures of health care resource use

Participants' use of health care for back pain during the year following randomization will be measured using automated utilization data, interview data on out-of-plan utilization, and records for each visit to the study massage therapists. The automated utilization data will provide information about all provider visits and hospitalizations at health plan facilities or paid for by the health plan. Visits for back pain can be identified by the diagnoses listed for every visit and hospitalization. Imaging studies of the lower back can also be identified by specific procedure codes.

Visits to non-study massage therapists and providers not covered by the health plan will be estimated from the interview data for the time period since the previous interview, i.e., the 10-week interview will request information about out-of-plan utilization since participants were randomized to study treatment, the 26-week interview will ask about the previous 16 weeks, etc. These data will permit determination of the percentage of participants in each treatment group who had any visits for low back pain during and following the intervention period, as well as calculation of the mean number of visits. Current use of medications of all types used for low back pain will be captured in the follow-up interviews.

Costs of back-related care will be estimated by assigning dollar values to each service. Costs of specific services (e.g., visits, imaging studies, medications) will be determined using data from Group Health's cost management information system which defines cost based on standard relative value units (RVUs) assigned to actual department RVUs produced. Costs of the massage interventions will be distinguished from the costs of all other back pain-related services to permit separate comparisons among the treatment groups of the costs of the interventions themselves, of the non-intervention back care costs incurred during the 10-week treatment period, and of the total back pain-related costs incurred over the 42 week period between completion of the study interventions and the end of the 52 week follow-up period.

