If we find a significant overall difference, we will localize the difference among the three groups using pairwise comparisons in accordance with our specific aims. For Aim 1, we will compare the RM group with the UC group. For Aim 2, we will compare the RM group with the FSM group. We will also compare the FSM group and the UC group, although this is not included as a specific aim.

We will consider interactions of treatment and the baseline value that would indicate the effect of treatment depends on status at baseline. We will also test for significant interactions of treatment with other variables (e.g., age, race, gender, and pain below the knee but not meeting criteria for sciatica) to determine if treatment differences are modified by these variables. To explore whether baseline characteristics predict which treatment performs better (Aim 3), we will examine our main outcome measures separately by subgroups using both tabular and graphical methods. We will begin with simple exploratory data analysis approaches, because we have no initial hypotheses about which characteristics will predict treatment success. Exploratory analysis will examine the univariate relationships between potential baseline predictor variables and outcomes of the treatments. We may also use more sophisticated statistical methods (e.g., latent class analysis) to identify individuals with different patterns of baseline characteristics that respond differently to the treatments.

We will also analyze secondary outcomes for Aims 1 and 2, including costs of back care, general health status (SF-36), depression, perceived stress, fear avoidance, disability days, and satisfaction with care. An analysis of costs may entail a transformation (e.g., log cost) but can be modeled using linear regression without a baseline value for costs since they will be unknown. We will adjust for age and other factors that may affect costs. We recognize that we will have low statistical power to detect even moderate cost differences among the groups. For binary outcomes (e.g., medication use) we will use logistic regression. Despite the multiplicity of analyses, we will focus our main analyses on treatment effects on each of the five outcome domains recommended for studies of back pain [8].

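### Baseline costs are called unknown, but that is true only of out-of-plan care: prior-year in-plan back-care use is obtainable and could serve as a covariate in the cost comparisons

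*Protocol article*

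**What the plan says.** Under Statistical Analysis, the article states that costs may be transformed and that the analysis "can be modeled using linear regression without a baseline value for costs since they will be unknown". It continues: "We will adjust for age and other factors that may affect costs". It then concedes that "we will have low statistical power to detect even moderate cost differences among the groups".

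Other sections describe the records available before randomization:

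- Inclusion and exclusion criteria: one of the two sources for exclusions is "automated data on ICD-9 diagnoses recorded during all visits over the previous year made by health plan members". Table 1 requires "Continuing member of Group Health" and "At least one primary care visit for back pain within the past 3-12 months", the latter taken from automated visit data.
- Recruitment procedures: the automated visit data identify candidates and remove those with excluding diagnoses in the prior year.
- Measures of health care resource use: "The automated utilization data will provide information about all provider visits and hospitalizations at health plan facilities or paid for by the health plan". Back-pain visits are found by diagnosis and lumbar imaging by procedure code. Costs are formed by assigning a value to each service from the health plan's cost system. Out-of-plan use comes from interviews and, at 10 weeks, covers the time since randomization.
- Assessment of outcomes, Table 3: there is no baseline entry for services outside the health plan.

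**The concern.** The article does not merely leave baseline cost unmentioned. It excludes it and gives a factual reason, and that reason does not fit its own account of the data for in-plan care.

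The exclusion also departs from the plan's general approach. The main outcome model includes the pre-randomization value of the outcome, and the sample-size section says that baseline covariates can improve precision and raise power. Costs are the stated exception, although they are the outcome for which the plan admits low power. At stake is a cost comparison noisier than it needs to be, when a plausible predictor lies in a data source the trial already queries.

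**Working it through.** **1. What is and is not known at baseline**

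| Component of back-care cost | Follow-up source | Before randomization |
|---|---|---|
| In-plan or plan-paid visits, hospitalizations, imaging | Automated data, valued service by service | Prior-year visit diagnoses already extracted for screening; the same valuation could be applied |
| Out-of-plan visits | Interviews, from randomization onward | Not collected |
| Study massage | Study visit records | Does not exist before randomization |

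So a baseline value of the whole cost outcome is unavailable, but its in-plan part is obtainable. A covariate need not match the outcome exactly to reduce residual variance.

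**2. Reproducing the plan's own figures**

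The article gives no power, SD or effect size for costs. The nearest figures are those for the Roland scale: 120 analysed per group, SD 4.65, two-sided 0.05.

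- Pairwise, 2.0 points: SE = 4.65 × √(2/120) = 0.600; 2.0/0.600 = 3.33; 3.33 − 1.96 = 1.37; power 91.5% (stated 91%).
- Omnibus, means 0/1/2: noncentrality = 120 × (1 + 0 + 1)/4.65² = 11.1; power 85.3% (stated 85%).

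The same two-means formula can therefore be used for costs on a standardized scale.

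**3. Effect of a baseline cost covariate**

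Let r be the correlation between prior-year in-plan cost and follow-up cost. It is not in the document, so 0.1 to 0.6 is an assumption. With linear adjustment:

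- residual SD = SD × √(1 − r²), so variance falls by r²;
- equivalent n per group = 120/(1 − r²);
- difference detectable with 80% power = (1.960 + 0.842) × √(2/120) × √(1 − r²), in SD units.

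The last column uses an assumed true difference of 0.25 SD.

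| r | Variance reduction | Equivalent n per group | Detectable difference (SD) | Power at 0.25 SD |
|---|---|---|---|---|
| 0 | 0% | 120 | 0.362 | 49.1% |
| 0.1 | 1% | 121.2 | 0.360 | 49.5% |
| 0.2 | 4% | 125.0 | 0.354 | 50.7% |
| 0.3 | 9% | 131.9 | 0.345 | 52.8% |
| 0.4 | 16% | 142.9 | 0.331 | 56.1% |
| 0.5 | 25% | 160.0 | 0.313 | 60.9% |
| 0.6 | 36% | 187.5 | 0.289 | 67.7% |

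The gain is negligible at r of 0.2 or less and becomes material at about 0.4 to 0.5.

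**The case against.** The strongest defence is that the statement is right for the outcome as defined. The cost outcome combines in-plan care, out-of-plan care and study massage, and no complete pre-randomization counterpart will exist. This stands as far as it goes. A reader might infer from the recruitment data that full baseline costs are already held; the documents do not support that. They show prior-year diagnoses being extracted. That prior-year services can also be costed is a strong inference from the service-based costing rules, not something stated.

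Second, no minimum length of prior enrolment is given, and supplementary recruitment may use older visits or magazine advertisements. Some participants may therefore lack a full prior year of data or a back-pain visit within it. This also stands, although for a member enrolled throughout the year, no visits is a known zero and not a missing value.

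Third, the plan's undertaking to adjust for other factors affecting costs could admit prior use. A reader might infer that this information is definitely discarded, and that is too strong. Still, the preceding sentence rules out a baseline cost value, and prior use is not named.

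Fourth, r may be low: costs are likely to be skewed, and selecting people for a recent back-pain visit narrows the spread of prior use. That is why only a range is given.

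Finally, a reader might fault the log transformation of costs, since a participant with no cost has no logarithm. The article says only that a transformation may be needed and gives the log as an example. The choice among transformation, generalized linear model and bootstrap is properly left to the analysis plan, so no error is shown there.

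**Conclusion.** The point holds in limited form. The stated reason for omitting baseline cost is correct for out-of-plan care and too broad for in-plan care. Adjusting for prior in-plan use is an inexpensive precision gain by the plan's own reasoning.

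Its size cannot be fixed from the document: variance falls by 1% to 36% for an assumed r of 0.1 to 0.6. This rests on linear adjustment, 120 analysed per group, and prior in-plan services being costable by the follow-up rules. Even at r = 0.6, power for an assumed 0.25 SD difference is only about 68%, so the cost comparison may remain underpowered.

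A reader might infer that the omission biases the cost comparison. It does not: under randomization, chance imbalance in prior cost is already reflected in the standard error. Costs are secondary, and the primary analyses are unaffected.

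**What to change.** In Statistical Analysis, replace the claim that baseline costs will be unknown with a statement that only out-of-plan baseline cost is unavailable. Prespecify in-plan back-related cost, or visit count, in the 12 months before randomization as a covariate in the comparisons of non-intervention back-care cost and utilization. Derive it with the diagnosis and costing rules used for follow-up. The cost of the massage intervention itself can be left out of this adjustment, since the study generates it and there is no reason shown why prior cost would predict it. State how members without a full prior year of enrolment will be handled.

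The cost is one further extract from records already queried for eligibility, plus a change of wording. There is no added burden on participants. Prior data will be incomplete for members enrolled for less than a year, and out-of-plan baseline cost stays unmeasured.
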